**Figure 3 f3:**
[figure not shown]
Structural equation model of food insecurity and insulin resistance. Additional co-variate demographics not depicted. Created with draw.io.

#### Microbiome exploratory analyses

The highly complex nature of microbiome data has led to a continuing evolution of analyses methods. We will use the next-generation microbiome bioinformatics platform QIIME 2 (122) as the standard analysis package from raw sequences to statistical evaluation of the cross-sectional saliva and the longitudinal (time series) stool microbiota study results. Additional methods such as LEfSe (Linear discriminant analysis Effect Size) (123) will be included in our analysis pipeline.

The compositional and zero-inflated nature of microbial community profiling data requires specialized, preferably non-parametric approaches for statistical analyses of associations with clinical or dietary variables. Due to high rates of periodontal disease in people with FI (124, 125) and PLWH (126, 127), we will explore correlations between oral microbiota profiles (composition and diversity) and insulin resistance, and whether self-reported measures of poor oral health, food insecurity, and chronic inflammation mediate these relationships. Additionally, we will explore whether GMB qualities (i.e., overall GMB diversity index; specific biomarker components, such as *Prevotella*, *Bacteroides* (128)) mediate the association between dietary intake (i.e., DII^®^; individual constituents such as fiber) and insulin resistance. The variance estimates and intraclass correlation coefficients from repeated measures of GMB and dietary recall data will be used to refine data collection and statistical analysis methods for the NOURISH-OK intervention (Aim 3).

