Additionally, the dietary patterns and periods of prolonged fasting caused by food insecurity may influence the gut microbiome (14), which is increasingly recognized for its role in systemic inflammation and insulin resistance within the general population (42, 43). Thus, food insecurity may exacerbate the consequences of HIV, since infection already disrupts gut homeostasis by reducing CD4+ Th17 and Treg cells in gut-associated lymphoid tissue, which increases intestinal permeability and microbial translocation (44), and drives immune activation and inflammation (45). AIDS history may be particularly detrimental to gut health (44), inflammation (33), and insulin resistance (33). HIV-related alterations in gut microbiome composition, dysbiosis, includes increases in pro-inflammatory *Prevotella* strains, and decreases in anti-inflammatory *Bacteroides* (33). A recent study linked a specific gut microbiome signature with metabolic dysfunction in PLWH, but lacked dietary data (46). Of the few studies that explore the influence of food insecurity or malnutrition on the gut microbiome and its metabolites (14, 47), none have included PLWH.

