### Prospective observational sub-study procedures

#### Replicate dietary intake and food security recalls

Upon completion of the cross-sectional study, participants will be randomly selected within their food security group for an invitation to participate in a 4-week observational sub-study. Elucidating the influence of food insecurity on dietary intake presents an important methodologic challenge because intake estimates from those with low and/or very low food security may potentially have higher error as compared to those with high or marginal food security. These differences in error may be due to wider fluctuations in food access throughout each month (101) and seasonally (102) for food insecure groups. Therefore, the primary purpose of the sub-study is to collect replicate dietary recalls to obtain a more precise estimate of usual dietary intake for each food security group, in addition to exploring how food security fluctuates from week-to-week. Trained interviewers will collect replicate dietary recalls and food security surveys *via* phone. At sub-study enrollment, subjects will receive a printed guide illustrating standard food units of measure for reference during phone calls to improve reporting accuracy.

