#### Final structural equation modeling

Finally, we will test our conceptual model using structural equation modeling, a method that allows simultaneous measurement of the strength and significance of predictor variables *via* direct and indirect pathways on a single outcome established *a priori* by theory (118). The theoretical framework draws from existing conceptual models (16, 119) that position physical and social community environments as risk regulators (119) for household food insecurity and its resulting individual nutritional and non-nutritional risk behaviors (16), which become embodied through pathophysiologic responses (119) (**Figure 1**). Sample size recommendations vary widely for studies that employ structural equation modeling, with lower estimates citing 200 cases for SEM models (118). We have selected a conservative sample size of 500, which exceeds more recent recommendations for up to 460 cases for multi-factor, multi-indicator models (120).

The SEM will simultaneously estimate direct and indirect effects of continuous exposure variables in the directional pathway of food insecurity and insulin resistance (**Figure 3**). Specifically, we will test the influence of upstream and social factors on food insecurity, and whether food utilization skills modify the association between community food access and food security. As an intermediate variable in the SEM, food security status will be used to predict insulin resistance using behavioral and pathophysiologic mediators with AIDS diagnosis as a potential effect modifier. We will use similar methods developed in our past research (121), including quasi-maximum likelihood estimation with Satorra-Bentler correction to measure direct and indirect paths between all variables. We will use Chi-square, Root Mean Square Error of Approximation (RMSEA), and Comparative Fit Index (CFI) to assess model fit. We will conduct invariance testing using AIDS status to compare model differences between those with and without AIDS diagnosis history. We will re-specify the model, if needed, using a theory-informed approach. Analyses will be conducted using R, Version 4.0.2.

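### Food insecurity is named a mediator of the oral microbiota–insulin resistance link although the framework places it upstream; separately, all stool samples follow the only QUICKI draw

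*Protocol article*

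**What the plan says.** Two mediation questions are set out in the protocol article under Microbiome exploratory analyses.

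- **Oral.** The article states "we will explore correlations between oral microbiota profiles (composition and diversity) and insulin resistance", and then "whether self-reported measures of poor oral health, food insecurity, and chronic inflammation mediate these relationships". The reason given is "Due to high rates of periodontal disease in people with FI (124, 125) and PLWH (126, 127".
- **Gut.** It states "we will explore whether GMB qualities" (diversity, and specific genera) "mediate the association between dietary intake (i.e., DII^®^; individual constituents such as fiber) and insulin resistance".

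The framework's direction appears in two other places. The introduction's section on downstream drivers says "the dietary patterns and periods of prolonged fasting caused by food insecurity may influence the gut microbiome (14". Under Final structural equation modeling, "food security status will be used to predict insulin resistance using behavioral and pathophysiologic mediators".

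On timing, the section on replicate recalls says "Upon completion of the cross-sectional study, participants will be randomly selected within their food security group" for the sub-study. Under Exploratory microbiome measures, saliva is taken at sub-study enrolment and stool weekly for four weeks. QUICKI is computed from the fasting glucose and insulin of the main-study blood sample. Table 3, which lists the sub-study measures, contains no glucose or insulin.

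**The concern.** A mediator lies between exposure and outcome. For food insecurity to mediate the oral link, oral bacteria would have to bring about household food insecurity. Reading the relationship the other way does not help, because insulin resistance would then have to cause food insecurity. The framework says neither. If food insecurity instead affects both oral microbiota and insulin resistance, part or all of their association is confounding, and the plan's wording would present that part as a pathway.

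For the gut model the issue is measurement order, not conceptual order. The proposed mediator is sampled after the outcome, so an association between the two cannot show that the microbiome came first.

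At stake is what the sub-study may conclude about mechanism. The main structural equation model does not depend on it.

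**Working it through.** The plan gives no effect size, alpha or power for these models, so there is no stated figure to reproduce. The check is of structure and timing, followed by an illustration.

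**1. Role of food insecurity**

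| Place in the protocol article | Position of food insecurity |
|---|---|
| Introduction, downstream section | Before the gut microbiome |
| Final structural equation modeling | Before the behavioural and pathophysiologic mediators, which precede insulin resistance |
| Microbiome exploratory analyses, rationale | Background to periodontal disease |
| Microbiome exploratory analyses, planned test | Between oral microbiota and insulin resistance |

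The fourth row conflicts with the first three. The structural equation section does call food security an intermediate variable, but between upstream social factors and insulin resistance, not downstream of microbiota. The introduction's statement concerns the gut. For the mouth, the direction comes from the periodontal rationale and the structural equation order.

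**2. Order of measurement**

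- Main visit: fasting draw, giving QUICKI (and CRP).
- Sub-study enrolment, afterwards: saliva. The gap is not stated and may be short.
- Four weekly contacts: a recall, then a sample of the next stool.
- No later glucose or insulin in Table 3.

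The start of the sub-study can be read as following each participant's main visit or the whole cross-sectional study. Either way, all stool samples follow the QUICKI draw.

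**3. Illustration, oral analysis (assumed paths)**

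Let food insecurity F raise the microbiota score M by *a* and lower QUICKI (Q) by *b*, in standardised units, with no effect of M on Q.

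- Marginal M–Q association: −*ab*.
- Mediation test as worded: slope of F on M (= *a*) times the coefficient of F in Q on M and F (= −*b*), giving −*ab*.
- Coefficient of M after adjusting for F: 0.

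The simulation used n = 100 (4 × 25), 4,000 replicates, linear models and joint significance at two-sided 0.05.

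| *a* = *b* | −*ab* | Simulated mean indirect effect | Declared significant | M coefficient adjusted for F |
|---|---|---|---|---|
| 0.2 | −0.04 | −0.040 | 25.1% | 0.001 |
| 0.3 | −0.09 | −0.089 | 71.2% | −0.002 |
| 0.4 | −0.16 | −0.161 | 96.2% | 0.000 |
| 0.5 | −0.25 | −0.249 | 99.8% | 0.001 |

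**4. Illustration, gut analysis (assumed paths)**

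Here diet lowers QUICKI by *c*, QUICKI affects the later-sampled microbiome by *d*, and the microbiome has no effect on QUICKI. The simulation settings are the same.

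| *c* = *d* | Mean false indirect effect | Declared significant |
|---|---|---|
| 0.2 | −0.008 | 3.7% |
| 0.3 | −0.024 | 11.4% |
| 0.4 | −0.055 | 35.8% |

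The gut risk is smaller than the oral one, and at the lowest paths it is below 5%.

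**The case against.** The case on the other side has weight.

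- **The work is labelled exploratory and no mediation model is specified.** True, and it limits the seriousness. But the role of food insecurity is stated, not left open, and the exploratory label does not reconcile it with the framework.
- **The Discussion concedes that a cross-sectional design cannot show time order, and that links may run both ways.** It does not mention that the microbiome is sampled after the outcome, or that food insecurity is placed downstream of microbiota. The Abstract already limits its temporal claim to food insecurity, diet and the gut microbiome, so part of the remedy is in place.
- **The fitted regression is the same whether food insecurity is called mediator or confounder.** Correct. The label decides whether the reader is told of a pathway or of confounding, and that is the whole of the point.
- **Repeat stools serve to characterise usual levels, and the delay may be short.** Reasonable, since replicate recalls have that purpose. It supports reporting an association but does not establish order.

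Several stronger readings are tempting and are not supported:

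- *Both models are ordered wrongly.* The gut model's conceptual order agrees with the framework.
- *All three oral mediators are misplaced.* Chronic inflammation fits the framework. Poor oral health is arguable: nothing shows that oral microbiota cannot act through oral disease, and Table 3 records food avoidance due to oral problems.
- *Mediated shares will be reported.* No proportion mediated is planned. A figure of 100% mediated would follow by construction from assuming no microbiota effect.
- *These results will set Aim 3 targets.* From these data the section takes only variance components and intraclass correlations to Aim 3. Only the general statement that Aim 1 informs later aims goes further.

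**Conclusion.** The point holds in two parts of unequal weight. The main part is that food insecurity is assigned as a mediator in the oral analysis, against the direction the article gives elsewhere. If it is a common cause, the test as worded reports confounding as an indirect effect. Over assumed paths of 0.2 to 0.5 that spurious effect is 0.04 to 0.25 in absolute size and is often significant at n = 100. The path sizes, the linear models and the absence of any microbiota effect are assumptions, so the range shows what can happen and does not estimate the bias in this study.

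The lesser part is that the gut mediator is measured after the only QUICKI, so its results are associational. Saliva also follows that draw, but with an unstated and possibly short gap, so the timing point is firmest for stool.

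The matter is moderate: it concerns an exploratory sub-study and leaves the primary structural equation model untouched.

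**What to change.** 1. In the oral analysis, treat food insecurity as an exposure or a confounder and adjust for it; remove it from the list of mediators. Chronic inflammation, and arguably poor oral health, may stay as candidate mediators.
2. In the gut analysis, keep the diet, gut microbiome, insulin resistance framing, but report microbiome–QUICKI results as adjusted associations without causal mediation claims. State that stool was collected after the fasting draw.
3. Keep temporal language for the weekly recall to next-stool analysis, where the order of measurement is right.

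No new data are needed. The cost is a change of analysis wording and a weaker mediation claim from a sub-study of 100 people.

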## Discussion

The NOURISH-OK study is a novel exploration of how the distinct psychological, dietary quality, and dietary quantity components of food insecurity may influence health risk behaviors and insulin resistance among PLWH. It challenges prevailing food insecurity research paradigms that traditionally emphasize one level of understanding (e.g., behavioral vs. molecular) by simultaneously considering environmental, psychosocial, behavioral, and biological factors in the pathogenesis of insulin resistance, and how food insecurity may amplify or dampen these pathways. Further, its conceptual framework incorporates the role of traumatic events as potential underlying contributors to food insecurity and its associated outcomes. Collectively, the first aim of the NOURISH-OK study is designed to provide HIV researchers, clinicians, and other stakeholders with key leverage point opportunities for building nutrition equity among PLWH, including development of evidence-informed food as medicine programs that address dimension(s) of underlying need.

In addition to elucidating the various potential mechanisms by which food insecurity shapes health risks, the NOURISH-OK study will support validation of dietary assessment measures in PLWH. These measures include dermal carotenoids as a biomarker for total carotenoid and total fruit/vegetable intake and construct validity of the DII^®^ as a predictor of inflammation in PLWH. Because carotenoids, fruits, and vegetables correlate with other nutrients that comprise the DII^®^ score and inflammatory markers, dermal carotenoids may be a useful non-invasive alternative to intensive dietary collection methods in future PLWH studies, including measures of intake and dietary intervention adherence. Although tested extensively in diverse populations (129, 130), this surrogate biomarker has not been studied among PLWH. The NOURISH-OK sub-study will further address methodologic gaps by exploring whether there are differences in dietary intake measurement error based on food insecurity status. If food security status is found to be related to measurement error, it will be paramount that future research investigating the role of food insecurity on dietary intake incorporate methods to adjust for this error. Furthermore, the sub-study’s oral and gut microbiome analyses will answer important questions about whether food insecurity is associated with distinct microbiome profiles and whether these profiles are attributable to diet and insulin resistance among PLWH. Finally, the NOURISH-OK study addresses additional methodologic gaps in health behavior research by including additional validation studies of other lifestyle behaviors among PLWH beyond diet, including self-reported tobacco (validated with serum cotinine) and perceived stress (validated with CRP).

An important limitation of the NOURISH-OK study’s first aim is the inability to establish temporal linkages among variables within the conceptual framework due to its cross-sectional design. Since the relationships between food insecurity and HIV-related outcomes may operate bidirectionally (9), additional research will be necessary to elicit a deeper understanding of complex relationships within the framework and to refine proposed mechanisms. The study’s second aim, comprised of qualitative inquiry with PLWH who experience food insecurity, will help to address this limitation by allowing the research team to triangulate data pertaining to potential directionality and context of significant pathways identified in Aim 1.

In closing, the NOURISH-OK promotes structural equity in HIV research by operating through a community-academic research partnership that directly involves PLWH at the decision-making table (131). These contextual factors will help to ensure current study activities incorporate community concerns and priorities, while simultaneously building capacity to plan and engage in future research that responds to evolving community needs.

## Ethics statement

The studies involving human participants were reviewed and approved by University of Oklahoma Health Sciences Center Institutional Review Board (study #12509). The patients/participants provided their written informed consent to participate in this study.

